### Contents and utilization of the neonatal kit

The integrated neonatal kit comprises a clean birth kit, 4% chlorhexidine solution, sunflower oil emollient, ThermoSpot™, Mylar infant sleeve, and a reusable, instant heat pack (Figure 1A). In addition, LHWs will be supplied with a handheld electric weighing scale (Figure 1B) with suspended cloth sling to weigh newborns. A detailed description of each kit component, its intended utilization and associated evidence is outlined in Table 1.

### Clean birth kit

Expectant mothers will be taught to provide the clean birth kit to the traditional birth attendant (TBA) or other individual conducting the delivery. If the expectant mother will be delivering her baby in a health facility, she will be instructed to take the clean birth kit to the facility where it may be used at the discretion of the health professional conducting the delivery.

### Chlorhexidine solution (4%)

Caregivers will be taught to apply a small amount of 4% chlorhexidine to a cotton ball and to dab the wet cotton ball onto the umbilical stump and surrounding area once a day from day 1 to day 10 of the newborn’s life.

### Sunflower oil emollient

The caregiver will be taught to take a small amount of oil into their hands and massage the oil into the newborn’s skin all over their body once a day from day 3 until day 28 of the newborn’s life. In this study, sunflower oil was mechanically extracted from raw sunflower seeds using an expeller press.

### ThermoSpot™

ThermoSpot™ is a small circular sticker that adheres to the skin and changes colour as temperature changes [25], allowing for continuous temperature monitoring. Five ThermoSpot™ stickers will be provided in each kit. Caregivers will be taught to apply one sticker to the axillary region of the newborn on their first day of life and to leave the sticker in place until it falls off on its own or until day 14 of life. If a sticker falls off, it will be replaced with a new one. The meaning of the appearance of each ThermoSpot™ will be explained to caregivers as well as the measures to be taken if the device indicates any sign of fever or hypothermia.

### Mylar infant sleeve

The caregiver will be taught that if ThermoSpot™ indicates moderate or severe hypothermia (Table 1), the non-electric warmer is to be activated and placed at the bottom of the Mylar sleeve and then the newborn is to be placed in the sleeve. Once the newborn is in the Mylar sleeve, the caregiver is to immediately take the child to the nearest health facility for further management.

### Reusable instant heat pack

If ThermoSpot™ indicates moderate or severe hypothermia, caregivers will be taught to activate the FDA-approved reusable instant heat pack and place it first inside a cloth pouch, and then at the base of Mylar infant sleeve. The activated heat pack holds its temperature for approximately 20 to 30 minutes.

### Handheld battery-operated weighing scale with suspended cloth sling

The scale will not be included with the kit but rather, one will be issued to each LHW in the intervention cluster. The LHW will be instructed to weigh the newborn at the first home visit after delivery. The newborn will be weighed twice and the average of these two weights will be recorded as the birth weight.

### Data collection and data management

Data collectors will be independent from LHWs and will be selected based on their high level of performance in previous work at the same study site. All data collectors will undergo three days of formal training where they will be taught the goals of the study, basic methodology, and provided with an in-depth understanding of all data collection forms. During training, data collectors will be required to conduct an observed interaction with a mother and newborn in the community to ensure standardization and quality data collection.

Data collectors will visit homes in the intervention and control clusters on day 1 (or as soon as possible after birth notification), 3, 7, 14, and 28 of life. To facilitate birth notifications, LHWs, community leaders, and the family of expectant women will be provided with instructions to call a study research officer within 24 hours of delivery. The research officer will notify the appropriate data collector. At the first visit, the data collector will administer a questionnaire to document the events surrounding delivery and the immediate post-natal status of the newborn and weigh the newborn. At each subsequent visit, the data collector will assess the newborn for primary and secondary outcomes through the administration of a questionnaire covering the events that took place since the last visit. Data collectors will be trained to identify danger signs and will refer the newborn to the LHW, triggering the appropriate cascade of events leading to referral to the most appropriate health facility. Data collectors will not be trained to treat outcome conditions. At any of these visits, the data collectors may be notified of the death of a baby. In the event of a newborn death, the parent will be given the choice of whether or not a verbal autopsy [26] can be performed. At 12 months of age, a proportion (approximately 450) of randomly selected children from each arm of the study will undergo a standardized assessment of neurodevelopment by a study worker trained in the application of the Bayley Scale of Infant Development III (BSIDIII) [27]. The data collector will be blinded to the arm of the trial to which the participant was randomized. The assessment takes up to 1 hour to administer, will be conducted in the homes of participants, and will be performed in the presence of a parent or caregiver. During the BSID standardized test, five key developmental domains of cognition, language, social-emotional, and motor and adaptive behaviour of the child are assessed [27].

Paper data collection forms will be delivered to the data management unit (DMU) on a daily basis where they will be entered in duplicate into electronic format. Prior to data entry, all forms will be checked for completeness and consistency and coded. In cases of inconsistency or missing responses, editors will flag the errors/omissions and consult data collectors for possible explanations. Research officers and supervisors will validate 5% and 2% respectively, of all home visits by recollecting data and comparing data collection forms with those filled in by data collectors. In cases where discrepancies exceed 20%, data collectors will be retrained. Databases will be developed using Microsoft FoxPro and will employ a range of consistency checks to minimize data entry errors.

### Data analysis plan

The primary outcome (death during the neonatal period) will be measured in both the intervention and control arms on days 1, 3, 7, 14, and 28 of a newborn’s life. This trial’s data will be analyzed as intention to treat using univariate and multivariate methods. Risk estimates will be adjusted for cluster allocation via generalized estimating equations using a log link between the binary response variable (binomial family) and the linear predictor, and unstructured correlations between observations. STATA version 13 will be used for all data analyses. Causes of death will be determined by physician review of verbal autopsy. Results will be presented in accordance with CONSORT guidelines.

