**Schematic diagram of trial activities.**

With an estimated live birthrate of 25 per 1000 population, baseline NMR of 42 per 1000 live births, and a population of ~35 live births per cluster, the randomization of 150 clusters, half to intervention and half to control, with 90% enrollment of eligible mothers and including up to a 10% loss to follow up will provide >80% power to detect a 40% reduction in mortality in the intervention compared to the control arm. All eligible women within a cluster will receive the same intervention. Since clusters are geographically separated from one another and families within each cluster are typically non-mobile, contamination is unlikely but to further avoid contamination, unused kit components will be collected from participants during their last data collection visit (day 28 of newborn’s life). Unused kit components will be also be collected in cases of stillbirths and child death after enrollment.

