### Randomization

Randomization will be performed on principal villages (clusters) stratified into two groups before randomization: villages with 1 LHW and those with more than 1 LHW. To balance cluster size, one large village will be excluded and the remaining villages will be randomized into two groups (intervention and control). To ensure that randomization is unbiased, a scientist who is not directly involved in the research project will perform the cluster-stratified randomization.

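### The primary GEE does not name the LHW stratum used in randomisation; if mortality differs between strata, its standard error will be slightly too large (minor)

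*Protocol article*

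**What the plan says.** The Randomization section of the protocol article says that villages are "stratified into two groups before randomization: villages with 1 LHW and those with more than 1 LHW". This is the only stratification factor.

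The Data analysis plan says that the data will be "analyzed as intention to treat using univariate and multivariate methods", and that "Risk estimates will be adjusted for cluster allocation via generalized estimating equations", with a log link, binomial family and unstructured correlation. I read the adjustment as accounting for clustering by village. The section does not mention the LHW stratum, lists no covariates, and does not say whether the univariate or the multivariate estimate is primary.

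The sample-size text (Study design, cluster definition and sample size) does not mention the stratification. It assumes "baseline NMR of 42 per 1000 live births", "a population of ~35 live births per cluster" and "the randomization of 150 clusters, half to intervention and half to control", and claims that this "will provide >80% power to detect a 40% reduction in mortality".

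**The concern.** Stratified allocation keeps the arms balanced on LHW number, so any mortality difference between the strata cancels out of the arm comparison. A model without the stratum does not know this. It leaves the difference in the between-village variation from which the robust standard error is computed. The estimate keeps the benefit of stratification, but its reported uncertainty does not show it.

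At stake is a little precision: wider intervals and larger p-values than the design warrants. A second, practical matter is that a univariate primary estimate that ignores the stratum would be consistent with the text as it stands, so the choice of primary model remains open on a term that the design itself determines.

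**Working it through.** **Inputs from the protocol article.** Control risk 0.042; 40% reduction, so intervention risk 0.042 × 0.6 = 0.0252; 75 clusters per arm; 35 live births per cluster, 90% enrolled and up to 10% lost, so m = 35 × 0.9 × 0.9 = 28.35 births per cluster and 75 × 28.35 = 2126 per arm.

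**Assumptions, because the article gives no figure.** Two-sided alpha of 0.05; strata of equal size; the same stratum rate ratio in both arms; stratum rates as shown; no other between-village variation unless stated.

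**Step 1: the plan's own figure.** With no clustering, SE = √[(0.042 × 0.958 + 0.0252 × 0.9748)/2126] = 0.00552. Power = Φ(0.0168/0.00552 − 1.96) = 86.1% (86.0% with a pooled variance under the null). With a design effect of 1 + 27.35 × ICC, power is 81.4% at ICC 0.005, reaches 80% at about 0.0065, and is 76.9% at 0.01. The claim of more than 80% therefore reproduces for a small ICC without any stratum term. The article states no ICC.

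**Step 2: excess standard error when the stratum is left out.** Work on the log risk ratio scale, which matches the log link.

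- Within-village term per arm, (1 − p)/(p × m): control 0.958/(0.042 × 28.35) = 0.8046; intervention 0.9748/(0.0252 × 28.35) = 1.3645; sum 2.1691.
- Stratum term per arm: d² × (m − 1)/m, where d is half the difference between the stratum rates divided by their mean. With a common rate ratio, d is the same in both arms, so the sum is 2 × d² × 0.9647.
- SE inflation = √(1 + stratum sum/2.1691) − 1.

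| Control stratum rates per 1000 | d | Stratum sum | SE inflation |
|---|---|---|---|
| 42 vs 42 | 0 | 0 | 0% |
| 36 vs 48 | 6/42 | 0.0394 | 0.9% |
| 33 vs 51 | 9/42 | 0.0886 | 2.0% |
| 30 vs 54 | 12/42 | 0.1575 | 3.6% |

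A shortcut that uses the control rate in both arms, √(1 + 27.35 × ICC) − 1 with ICC = (half difference)²/(0.042 × 0.958), gives 1.2%, 2.7% and 4.8%. It overstates the effect, because the lower planned risk in the intervention arm raises the within-village term there. Other between-village variation lowers the percentages further.

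**Step 3: power cost.** On the risk difference scale, let W be the within-stratum variance of a cluster mean summed over the two arms, and T the same with the between-stratum part added. Power with the stratum is Φ(0.0168/√(W/75) − 1.96). Power without it is Φ((0.0168 − 1.96 × √(T/75))/√(W/75)), because the true spread is unchanged and only the reported SE grows.

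Example, rate ratio 2.0 (28 vs 56 per 1000 in control; 16.8 vs 33.6 in intervention): W = 0.002276 and T = 0.002276 + 0.014² + 0.0084² = 0.002543. The SEs are 0.005509 and 0.005823. Power is Φ(1.089) = 86.2% with the stratum and Φ(0.978) = 83.6% without.

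| Stratum rate ratio | Without stratum | With stratum | Without, k = 0.25 | With, k = 0.25 |
|---|---|---|---|---|
| 1.0 | 86.1% | 86.1% | 83.8% | 83.8% |
| 1.25 | 85.8% | 86.1% | 83.6% | 83.9% |
| 1.5 | 85.2% | 86.1% | 82.9% | 83.9% |
| 2.0 | 83.6% | 86.2% | 81.3% | 84.0% |

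Here k is an assumed coefficient of variation of the true rate between villages of the same stratum. A 30:70 split of the strata gives similar results.

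**Step 4: simulation.** 400 trials per setting, log-link GEE with Poisson working variance, independence correlation and robust SE (a stand-in for the stated binomial, unstructured model). The treatment estimate had the same empirical SD with and without the stratum. The mean model SE without and with it was 0.1741 and 0.1703 at ratio 1.5 (2% larger without), and 0.1784 and 0.1692 at ratio 2.0 (5% larger). With 400 replicates the empirical SD itself carries an error of about 1/√800 = 3.5%, so the run confirms the gap between the two model SEs; that the smaller one is correct rests on the algebra.

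**The case against.** The strongest objection is that the article does not exclude the stratum. It promises multivariate methods without a covariate list, and such a list is commonly left to a full protocol or analysis plan that is not shown. That stands against a reader who infers that the plan has decided to leave the stratum out: the text supports only that the stratum is not named. It does not remove the point. The article goes into detail on link, family and correlation, yet leaves open the one covariate that its own randomisation determines.

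Second, nothing in the article shows that mortality differs by LHW number. Each LHW serves about 210 households (Study setting), so villages with several LHWs are larger but have much the same nominal coverage per household. The only balancing aim that the Randomization section gives concerns cluster size. This stands in full, and it makes the loss conditional.

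Third, the harm is small and in the conservative direction. This also stands. A reader might infer a biased estimate, a false-positive risk or a failed power claim, and none of these follows. Whether the power margin is thin depends on an ICC that the article does not state.

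**Conclusion.** The point holds as a minor one. The trial randomises within two LHW strata, and the stated primary model does not carry that factor. If mortality differs between the strata, the reported standard error is about 1% to 4% too large for assumed control rates from 36 vs 48 to 30 vs 54 per 1000 (about 5% at a rate ratio of 2.0 in the simulation). The corresponding power cost is 0 to about 3 points for rate ratios of 1 to 2. If the strata do not differ, there is no loss.

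Intervals and p-values would be mildly conservative. The treatment estimate is not biased, type I error is not inflated, and no printed figure is wrong because of this. The sizes rest on equal strata, 28.35 births per cluster, a common stratum rate ratio in both arms, and little or no other between-village variation. The documents cannot confirm the stratum rates.

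**What to change.** In the Data analysis plan, state that the primary GEE for neonatal mortality includes the LHW stratum (1 vs more than 1) as a fixed covariate, and that this model gives the primary estimate. If the full protocol or analysis plan already says so, a cross-reference is enough.

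Do the same for secondary outcomes that are actually compared between arms. Hypothermia and hyperthermia are defined by ThermoSpot, a kit item, and the article describes no such reading in control clusters. The term has no role there unless a between-arm comparison is planned.

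The cost is one binary term, known for every village before randomisation. No new data and no change to the sample size are needed.

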### Study design, cluster definition and sample size

This study is designed as a cluster randomized, pragmatic, open label controlled intervention trial that will be conducted within the existing health care infrastructure in Pakistan. Specifically, both the intervention (neonatal kit) and control (standard care) will be delivered to participants by LHWs (Figure 3). A cluster has been defined as a principal village and its associated LHWs.

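### The primary mortality GEE specifies an unstructured working correlation for villages of interchangeable newborns; the result depends on record order and, where the model fits, type I error is about 8–12% rather than 5%

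*Protocol article*

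**What the plan says.** The protocol article's Data analysis plan describes one inferential model: "Risk estimates will be adjusted for cluster allocation via generalized estimating equations using a log link between the binary response variable", with "binomial family) and the linear predictor, and unstructured correlations between observations". It adds that "STATA version 13 will be used for all data analyses". It defines no order of newborns within a village and gives no alternative if the model cannot be fitted.

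The section on study design, cluster definition and sample size states that "A cluster has been defined as a principal village and its associated LHWs" and plans for "a population of ~35 live births per cluster, the randomization of 150 clusters, half to intervention and half to control". Table 2 makes the primary outcome all-cause death by day 28, so each live birth contributes one yes/no value. The Randomization section stratifies into "villages with 1 LHW and those with more than 1 LHW" and leaves out one large village to even up sizes, so village sizes will differ.

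**The concern.** An unstructured matrix gives every pair of positions in a cluster its own correlation. That makes sense when position means the same thing in every cluster, as with visit 1 and visit 2 of one patient. Newborns in a village are exchangeable: the correlation of the third newborn with the seventeenth has no meaning across villages, and who is third depends on how the file is sorted.

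The matrix is also far too large for the information available. Noise in hundreds of estimated correlations enters the weights of the estimating equations. This makes the estimate more variable, and the sandwich standard error does not capture the extra variability. The confidence interval and p-value for the primary outcome are at stake, and the sponsor intends the result to inform policy.

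**Working it through.** **Inputs from the protocol article.** 150 villages, 75 per arm; about 35 live births per village; 90% enrolment; up to 10% loss; control mortality 0.042; target reduction 40%, giving 0.042 × 0.6 = 0.0252.

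**Assumed, because not stated.** Two-sided alpha 0.05; intracluster correlation (ICC) 0.001–0.01; the spread of village sizes.

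**1. The plan's own power figure.** Analysed births per village: 35 × 0.9 × 0.9 = 28.35. Per arm: 75 × 28.35 = 2126. For 0.042 against 0.0252 the power is 86.0% with no clustering. Dividing by the design effect 1 + 27.35 × ICC gives 81.4% at ICC 0.005 (design effect 1.137) and 76.9% at ICC 0.01 (1.274). The claim of more than 80% reproduces for an ICC up to about 0.006, so these inputs are a fair basis for the check.

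**2. Size of the matrix.** The number of correlations is m(m−1)/2:
- m = 28: 28 × 27 / 2 = 378
- m = 35: 35 × 34 / 2 = 595

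With unequal villages, the largest one sets the dimension.

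**3. Information per correlation.** Ignoring the small within-village correlation, expected joint deaths for one pair of positions over 150 villages are 150 × 0.042² = 0.26. The chance of none is (1 − 0.042²)^150 = 0.77. Under the planned effect, the expectation falls to 75 × 0.042² + 75 × 0.0252² = 0.132 + 0.048 = 0.18.

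**4. Type I error, equal village sizes.** Log-binomial GEE, both arms at 0.042, beta-binomial outcomes, 1000 replicates per row, Wald test with sandwich standard error. Unstructured results are among fitted replicates. Monte Carlo error is about 0.7 points at a 5% rate.

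| m | ICC | Unstructured fitted | Unstructured type I | Mean SE / true SD | Exchangeable type I |
|---|---|---|---|---|---|
| 28 | 0.001 | 999 | 8.9% | 0.140 / 0.159 | 4.1% |
| 28 | 0.005 | 996 | 9.2% | 0.148 / 0.170 | 4.3% |
| 28 | 0.01 | 989 | 11.1% | 0.157 / 0.191 | 5.5% |
| 35 | 0.005 | 980 | 11.9% | 0.134 / 0.166 | 6.2% |
| 35 | 0.01 | 950 | 11.2% | 0.145 / 0.182 | 4.5% |

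The standard error accounts for the excess. In the second row 0.148 / 0.170 = 0.87, and 2 × (1 − Φ(1.96 × 0.87)) is about 8.8%, close to the 9.2% observed. A separate set of runs gave 7.6% (m = 28, ICC 0.001), 9.4% (m = 28, ICC 0.005) and 10.3% (m = 35, ICC 0.005), against 4.4–5.9% for exchangeable.

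**5. Fit with unequal sizes** (Poisson around 28, or coefficient of variation 0.4). When each correlation is averaged over the villages that contain the pair, 0 of 1000 replicates fitted in each of four scenarios: a correlation exceeded 1 or the matrix was not positive definite. When each entry is divided by the total number of villages, 995 and 998 of 1000 fitted at ICC 0.005, with type I error 9.2% and 9.7%; exchangeable gave 5.4% and 5.7%.

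**6. Efficiency under the planned effect** (m = 28, ICC 0.005). The SD of the log risk ratio is 0.200 unstructured and 0.183 exchangeable; rejection rates are 78.0% and 80.8%. The unstructured matrix brings no gain in power to set against its inflated error.

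**7. Record order.** In one simulated data set, newborns were reshuffled within villages 200 times. Fourteen orderings could not be fitted. Across the other 186 the risk ratio ran from 0.48 to 0.96 (5th to 95th percentile 0.56 to 0.75) and p from 0.00006 to 0.87. The exchangeable model gives one answer for these data: exp(−0.393) = 0.67, SE 0.193, z = 2.04, p about 0.04.

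**The case against.** The article condenses a fuller protocol, and details such as the data layout, the variance estimator and a convergence fallback are commonly left to an analysis plan. That is right, and their absence is no finding. The word unstructured is different: it is a positive choice for the primary model, and it is the wrong one for this cluster.

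None of the simulations ran in Stata, the software the plan names. This limits what can be said about fitting. A reader might infer that the model generally cannot be fitted. That is not established: failure ranged from under 1% to 100% according to how the software scales the pairwise moments and how village sizes vary. It did not rise simply with spread, since villages of two sizes, 19 and 38, gave 33 non-converged fits of 286 (about 12%). A failed fit is also visible and cannot itself produce a false positive.

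A reader might also take about 13% as the headline error rate. That value occurred in one small run (286 replicates, m = 35) and lies above the range in the larger runs.

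Finally, since mortality "will be measured in both the intervention and control arms on days 1, 3, 7, 14, and 28", a reader might take the observations to be the five visits of one infant, with village clustering ignored. The text does not support this. The same sentence that names the correlation structure adjusts for cluster allocation, and the endpoint is a single death per newborn.

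**Conclusion.** The specification is wrong as written. It requires 378 to 595 correlations from 150 villages with about 0.26 expected joint deaths per pair, and it makes the primary estimate depend on an arbitrary sort order. Whether it can be fitted depends on software and village-size spread. Where it fits with equal village sizes, type I error is roughly 8–12% against a nominal 5%, because the robust standard error is too small; exchangeable stays at about 4–6%.

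These rates assume an ICC of 0.001–0.01 and a two-sided 5% test. The inflation appeared at every ICC tried, including 0.001. The order dependence needs no simulation: it follows from applying the matrix to units that have no order. Because the phrase governs the primary test, it should be corrected before analysis.

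**What to change.** In the Data analysis plan, replace the unstructured correlation with: one record per live birth (dead or alive at day 28), the principal village as the GEE cluster, an exchangeable working correlation with independence as the fallback, and robust (sandwich) standard errors. Independence with robust standard errors also held its level in the same runs, at 4.1–6.2%. A Poisson family with log link and robust standard errors, for use if the log-binomial model does not converge, is a sensible optional addition that targets the same risk ratio.

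The cost is one sentence. It needs no new data and no change to design, endpoint or conduct.
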